| Outcomes                            |                         |                               |                       |                                                                                                                                                                           |          |          |                      |          |          |                         |           |           |                       |
| PMC uptake                                 |                         |                               |                       | X                                                                                                                                                                         | X        | X        | X                    | X        | X        | X                       | X         | X         |                       |
| Clinic visits, Adverse events              |                         |                               |                       | Passive surveillance in clinics in the catchment area, 26 weeks from 0-26 weeks (clinical malaria and other acute illnesses) (RDT/smear, Hb, and other tests as required) |          |          |                      |          |          |                         |           |           |                       |
| Hospitalisation                            |                         |                               |                       | Passive surveillance for hospital admission in the catchment area, 26 weeks from 0-26 weeks                                                                               |          |          |                      |          |          |                         |           |           |                       |
| Vital status                               |                         |                               | X                     | X                                                                                                                                                                         |          |          |                      | X        |          |                         |           | X         | X                     |
|                                            |                         |                               |                       |                                                                                                                                                                           | X        | X        | X                    |          | X        | X                       | X         |           |                       |
| Patient costs                              |                         |                               | X                     |                                                                                                                                                                           |          |          |                      |          |          |                         |           |           | X                     |

Visit #1: Enrolment and randomisation at discharge

Visit #2 #3#4: Home visits at 6, 10 and 14 weeks after enrolment to assess uptake of the 1st, 2nd and 3rd treatment course of the PMC study drugs respectively.

Visit #5: at 3.5 months after enrolment. This is the close out assessment.

---

- a. Children can be pre-study screened any time between hospital admission and enrolment. The figure of -4 days is provided for illustration purposes only.
- b. Visit window= number of days an actual subject visit may fall outside of the planned protocol schedule visit to still meet protocol requirements. DP should be given at least 4 weeks apart.
- c. MS, malaria smear. This will be collected for research purposes only, and read days to weeks later. Malaria smears will not be used for point of care. If participants are symptomatic (e.g. fever) an RDT will be taken for point of care.
- d. VP=vena puncture. FP=finger prick, DP=dihydroartemisinin-piperaquine, , Hb=haemoglobin, MS=malaria smear, Pf=Plasmodium falciparum

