**Study Interventions:** All children will receive Dihydroartemisinin-piperaquine (3-day treatment courses, given 2, 6 and 10 weeks after discharge) either: a) at discharge + SMS Reminder; b) at discharge + No SMS Reminder; c) at discharge + HSA Reminder; d) at OPD + SMS Reminder; or e) at OPD + No SMS Reminder

**Outcome Measures:** Primary: 100% of PMC drugs uptake (defined as administration of **all** 3-day treatment courses, given 2, 6 and 10 weeks after discharge) assessed by unannounced spot checks.

**Follow-up procedures:** Children will be followed up for 15 weeks by passive case detection in 2 phases: Pre-PMC (2 weeks between hospital admission and 2 weeks post-discharge); PMC (2-14 weeks post-discharge)

**Sample Size:** A sample size of 75 children per arm (375 total children) allows for a detection of 25% increase in uptake from 50% to 75% with 10% loss to follow-up (power 90%,  $\alpha=0.05$ ).

**Data Analysis:** The % of children receiving IPTpd according to schedule will be compared by relative risks (95% CI), adjusted for prognostic factors at baseline using log binomial or Poisson regression with adjustment for cluster effects

**Partner Institutions:** University of Bergen; Makerere University; KEMRI-CDC, Kenya; University of Minnesota; Liverpool School of Tropical Medicine; London School of Hygiene & Tropical Medicine; Imperial College London; University of Amsterdam; US Centers for Disease Control and Prevention, University of North Carolina, and University of Massachusetts.

Table1 : Study treatment and phases

| [figure not shown] |                                                     |                                                                                                                                                                                                                              |
|-------------------------------------------------------------------------------------|-----------------------------------------------------|------------------------------------------------------------------------------------------------------------------------------------------------------------------------------------------------------------------------------|

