## 8.3 SAMPLE SIZE

Although a factorial design will be used, only the main effects of PMC mode of delivery and the “use of SMS/HSA reminders” are of primary interest. There are five arms in total as described above such that each of the four intervention arms will be compared to the control arm (Arm 1: Mother given at discharge without SMS reminder). Each village cluster contributes 2 to 4 children/year on average with severe anaemia. Thus, the cluster sizes vary and we have accounted for this in sample size calculations in order to achieve the number of clusters that would have enough power to detect the desired difference. The sample size calculation has been adjusted in the design effect using the coefficient of variation method [11-13]. This has assumed that the cluster sizes will be uniformly distributed between 2 and 4 children i.e. U[2,4]. This gives a mean cluster size of 3 children per village per year and a standard deviation of cluster sizes of 0.58. Hence the coefficient of variation of cluster sizes (CV) is  $0.58/3 = 0.19$  and  $CV^2 = 0.036$ . Assuming an

intra-cluster correlation coefficient (ICC) of 0.1 and allowing for 10% loss-to-follow-up, a sample size of 25 clusters of an average of 3 children per village (75 children per arm, N=375 overall (for 125 clusters for the 5 arms)) has 80% power to detect a 25% absolute increase in uptake from an estimated 50% in the OPD and delivery at home groups to 75% in the arms supported by SMS reminders ( $\alpha=0.05$ ). The ICC of 0.1 is slightly more conservative than the ICC in a previous trial of delivery approaches for IPTc in the Gambia (0.08)[14].

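### Section 4.2 claims 90% power for 75 children per arm; section 8.3 gives 80% on the same inputs, and only the 80% reproduces

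*Protocol*

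**What the plan says.** Section 4.2 (Narrative Protocol Summary), for 75 children per arm and 375 in total: "25% increase in uptake from 50% to 75% with 10% loss to follow-up (power 90", that is, 90% power, with alpha 0.05. That sentence mentions no clustering, although the same summary describes a cluster randomised trial and plans an analysis adjusted for cluster effects.

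Section 8.3 (Sample Size): "75 children per arm, N=375 overall (for 125 clusters for the 5 arms)) has 80% power to detect a 25% absolute increase in uptake". The contrast is "from an estimated 50% in the OPD and delivery at home groups to 75% in the arms supported by SMS reminders", again at alpha 0.05. The inputs are an "intra-cluster correlation coefficient (ICC) of 0.1 and allowing for 10% loss-to-follow-up", and "a sample size of 25 clusters of an average of 3 children per village". On varying village size: "This gives a mean cluster size of 3 children per village per year and a standard deviation of cluster sizes of 0.58".

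Section 11.7.1 gives a third statement with a different layout (19 clusters of 5 per arm, 95 per arm, N=380, 20% loss). It also states 80%.

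No section says whether alpha is one- or two-sided, and nothing explains the 90%.

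**The concern.** Every input that sections 4.2 and 8.3 share is identical: 75 per arm, 375 overall, 50% against 75%, 10% loss, alpha 0.05. The stated powers differ by ten points, so at least one is wrong. The section that states the clustering assumptions gives the lower figure, which suggests that the summary took its figure from a calculation for individually randomised children.

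The stake is how a null result is read. At 90% power a true 25-point gain is missed one time in ten; at 80%, one time in five. Section 7.1 says the trial is meant to inform policy on delivery. A reader who sees only the summary could take a non-significant SMS or HSA comparison as firmer evidence of no benefit than the design supports.

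**Working it through.** **Inputs (section 8.3).** p1 = 0.50, p2 = 0.75, difference 0.25; 75 per arm; 10% loss, leaving 75 × 0.9 = 67.5; ICC 0.1; mean cluster size 3; cluster sizes uniform on 2 to 4, so SD = 2/√12 = 0.577, CV = 0.577/3 = 0.192 and CV² = 0.037 (the protocol rounds to 0.19 and 0.036). Comparison of one arm with Arm 1, equal allocation. *Assumption:* alpha 0.05 is two-sided.

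**Formulas.** p1(1−p1) + p2(1−p2) = 0.25 + 0.1875 = 0.4375, square root 0.6614. With p̄ = 0.625, 2p̄(1−p̄) = 0.46875, square root 0.6847.

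- Unpooled: power = Φ(0.25√n / 0.6614 − 1.96)
- Pooled: power = Φ((0.25√n − 1.96 × 0.6847) / 0.6614)
- Design effect, coefficient-of-variation form: 1 + ((1 + CV²)m − 1) × ICC

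**Step 1: reproduce section 8.3.** Design effect = 1 + (1.037 × 3 − 1) × 0.1 = 1.211. Effective n = 67.5/1.211 = 55.7 per arm. Unpooled: Φ(2.822 − 1.96) = 80.6%. Pooled: Φ((1.866 − 1.342)/0.6614) = 78.6%. The stated 80% is reproduced.

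**Step 2: try to reproduce section 4.2.**

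| Case, two-sided 0.05 | n per arm | Pooled | Unpooled |
|---|---|---|---|
| 10% loss and clustering | 55.7 | 78.6% | 80.6% |
| 10% loss, no clustering | 67.5 | 85.9% | 87.4% |
| No loss, no clustering | 75 | 89.3% | 90.5% |

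Only the last row is near 90%, and it leaves out the loss named in the same sentence as well as the clustering.

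**Step 3: what 90% would need on the inputs of section 8.3.** Unpooled: (1.96 + 1.2816)² × 0.4375/0.0625 = 73.6 evaluable; × 1.211/0.9 = 99 per arm. Pooled: 77 evaluable; × 1.211/0.9 = 104 per arm. Either way, well above 75.

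**Step 4: sensitivity to the village count.** Sections 4.2, 8.2 and 8.7.4.2 name 90 villages, or 18 per arm. Assume that 375 children are spread over them and the CV is unchanged.

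- 75/18 = 4.17 children per village: design effect 1 + (1.037 × 4.17 − 1) × 0.1 = 1.332, effective n = 67.5/1.332 = 50.7, power 74.6% (pooled) to about 77% (unpooled).
- Cluster size after loss, 67.5/18 = 3.75: design effect 1.289, effective n 52.4, power 76.0% to 78.1%.

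**The case against.** **It is one parenthesis in a synopsis.** Section 8.3 gives its assumptions and is right on them, and section 11.7.1 also says 80%. Correcting the 90% changes no sample size, allocation or analysis. Results will be reported as relative risks with 95% confidence intervals, so the precision will be visible. This stands as a limit on the consequences. It does not make the stated power correct.

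**Sidedness is not stated.** A reader might infer that 90% is out of reach even when clustering is ignored, or that it can arise only from 75 independent children. Neither holds without the two-sided assumption: one-sided 0.05 with 10% loss and no clustering gives 92.0–92.8%. But a one-sided test does not rescue the summary. With loss and the design effect it gives 87–88%, which is below 90% and does not match the 80% in section 8.3. No single sidedness supports both figures. The suggestion that the 90% came from an individually randomised calculation is plausible, but the document does not say so.

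**Perhaps the 90% refers to a pooled factorial main effect.** Pooling two arms against two (150 against 150, 10% loss, design effect) gives about 97.5%, so this does not explain it either.

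**Section 8.3 is not alone in allowing for clustering.** Section 11.7.1 also uses an ICC of 0.1 and names the design effect. That is correct, and it is a further statement at 80%.

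**Conclusion.** The contradiction is certain and needs no calculation. The figure at fault is the 90% in section 4.2. On the trial's own inputs, two-sided, power is 79–81%, so the summary overstates it by about ten points and halves the apparent type II error. The range reflects the choice of variance formula. The result rests on a two-sided 0.05 test, one arm against Arm 1, ICC 0.1, CV 0.19, and 25 villages of 3 children per arm.

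Two stronger readings are not supported. The first is that section 8.3 is itself miscalculated: on its stated inputs it is sound. The second is that section 4.2 should simply carry a figure in the mid-70s because 90 villages will be used. The protocol plans 90 villages in some places and 125 clusters in section 8.3, so the final number is not settled. The lower figure also depends on how 375 children fall across 90 villages. That is a separate inconsistency. Nor is there evidence that the 90% has spread: the registration table in section 4.1 gives the target of 375 and no power.

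**What to change.** In section 4.2, replace the 90% with the section 8.3 figure of 80%, and state beside it the ICC of 0.1, the design effect of about 1.21 and that alpha is two-sided. Add the sidedness to section 8.3 as well. The cost is a line of text in each section and a less favourable headline figure; trial conduct does not change.

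Separately, reconcile the village count. If 125 clusters stands, 80% stands. If 90 villages stands, restate the power in sections 8.3 and 4.2 together, at roughly 75–78% on the assumptions shown, so that correcting one section does not create a new contradiction with the other. That second step costs more than a line, because the section 8.3 calculation has to be redone with the cluster sizes actually expected.

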## 6 BACKGROUND

Children hospitalized with severe anaemia in Africa are at high risk of readmission or death within 6 months after discharge. Malaria remains a major cause of severe anaemia in these settings [1]. A recent multi-centre, randomized, placebo- controlled trial was carried out to determine the impact of administering malaria chemoprevention with Intermittent Preventive Therapy post-discharge (IPTpd) on mortality and readmissions due to severe anaemia among 1441 children <5 years of age with severe anaemia in Malawi [2]. The findings showed that provision of 3 months of chemoprevention with 3 full treatment courses of Artemether Lumefantrine (AL), given in-hospital for initial malaria episode and at 1 and 2 months post-discharge, prevented 31% (95% CI 5-50,  $P=0.02$ ) of deaths or readmissions due to severe anaemia or severe malaria (composite primary endpoint) by 6 months post-discharge and 41% by 3 months (95% CI 10-62,  $P=0.014$ ). The beneficial effect was in addition to the initial effect from the standard AL treatment course provided at discharge and in addition to any protective effect by insecticide treated nets (ITNs) [2]. These results are consistent with earlier findings from The Gambia, which showed that in children with severe anaemia, chemoprevention (as monthly IPT with SP or as weekly prophylaxis with Pyrimethamine-Dapsone) targeted during the malaria transmission season halved the rate of clinical malaria and reduced all-cause hospital readmission by 78% in one trial, and recurrence of severe anaemia by 78% in the other [3, 4]. These data are scarce, but indicate that IPTpd in the post-discharge period may potentially provide substantial health benefits.

IPT is the administration of a full treatment course of long-acting antimalarials at pre-defined time intervals irrespective of a patient's malaria status. IPT clears existing infections and provides prolonged prophylaxis against new infections [5]. The World Health Organisation's (WHO) recommended malaria control strategies include IPT for pregnant women (IPTp) and for infants (IPTi) and children living in areas with seasonal malaria transmission (IPTc).

### 6.1 High risk of severe anaemia rebound after discharge:

Severe anaemia is a leading cause of hospital admissions in Africa contributing substantially to paediatric mortality. Our recent case-control study in Malawian children indicated that children aged <5y admitted with severe anaemia are not only at high risk of dying during the acute phase in-hospital (6%) but also for several months after they leave hospital: 8% had died by 6 months post-discharge, which is nine times higher than the mortality in community-based, age matched children with mild anaemia [1, 6]. A further 8% were readmitted with rebound severe anaemia [6]. Similar rates of post-discharge morbidity and mortality are seen in western Kenya, where 17.9% of children <5y admitted with severe anaemia died or were readmitted by 6 months ([name] et al, unpublished observations), while in Uganda as many as 36.5% died or were readmitted within 6 months ([name] et al, unpublished data). Hospitalised children with severe anaemia are particularly at risk within the first 3 months post-discharge, likely due to a combination of environmental, behavioural, nutritional and genetic risk factors [3, 4, 6].

## **6.2 Malaria as a cause of post-discharge severe anaemia and mortality**

Since most post-discharge mortality in children occurs at home, the causes of death have rarely been assessed. However, previous observational studies in western Kenya and a recent intervention study in a high transmission area in Malawi showed that, malaria in the post-discharge period is an important contributor responsible for a slow haematological recovery, rebound severe anaemia and morbidity. Many children in these areas experience episodes of new or recrudescent malaria infections after discharge which negates the initial rise in haemoglobin (Hb) achieved by blood transfusion in hospital. Haematological recovery from malaria-associated anaemia is known to take at least 6 weeks. This period may be prolonged in those with persistent or new malaria infections due to on-going red cell destruction and red blood cell production failure.

## **6.3 Treatment strategies for prevention of malaria and haematological recovery post-discharge:**

Standard treatment for severe anaemia in many countries in sub-Saharan Africa (SSA) consists of a blood transfusion combined with (presumptive) IV anti-malarial treatment (quinine or artesunate) plus antibiotics if bacterial infections are suspected. Once children have stabilised and can be switched to oral treatment this is completed with short courses of 3-day treatment with artemisinin-based combination therapy (ACT), usually artemether-lumefantrine (AL). Children are often discharged with a short course of iron and folate, typically with no scheduled follow-up [7].

Creating a prophylactic time-window post-transfusion, is suggested to allow time for the bone marrow to recover, resulting in a more sustained haematological recovery post-discharge. Data from a previous study in Malawi show that this process takes 2-3 months in children with severe anaemia [1]. Recently, the use of IPT in children with severe anaemia during the rainy season reduced clinical attacks of malaria by more than 80% in areas with highly seasonal transmission.

## **6.4 Proposed PMC delivery mechanisms trial**

The PMC delivery mechanisms and health services trial is one of the five Major Activities (MAs) that will address gaps in knowledge before the Global Malaria Programme (GMP) of WHO would consider whether PMC should be recommended as a strategy for the post-discharge management of children with severe anaemia. The main objective is to determine the uptake, effectiveness, cost-effectiveness, acceptability and feasibility of two different mechanisms for delivering IPTpd: facility vs community-based approaches and examining the added role of mobile phone text message reminders.

## **6.5 Rationale for choice of methods**

In the past two decades, most research on severe anaemia and severe malaria focused on reducing in-hospital mortality. Our observations suggest that a major, potentially preventable, component of the burden occurs after discharge and that a proactive approach using PMC could offer substantial public health gains. This is a priority area for research since no strategy specifically addresses this high-risk post-discharge period. Although PMC is a simple intervention, implementation requires appropriate delivery mechanisms as treatment must be administered for 3 days at different pre-specified intervals post-discharge. Whereas IPT strategies in infants and pregnant women are

delivered through the expanded programme on immunisation and antenatal clinics, delivery of PMC will require new systems to be established that are sustainable and cost-effective. Delivery of IPTc to children through community health workers has been shown to be feasible and well accepted in rural West Africa [8, 9]. In Malawi, there are health systems that include village health volunteers (VHVs) and Health Surveillance Assistants who could deliver PMC or schedule post-discharge visits to clinics or hospital outpatient departments for subsequent PMC doses. Since PMC targets a very high-risk group of hospitalised children who already have contact with the health-care system, the point of entry is already established [10].

## **7 STUDY OBJECTIVE**

### **7.1 Primary objective**

The primary objective of the trial is to determine the optimum PMC delivery mechanism by comparing community- versus health facility-based strategies in order to inform policy

### **7.2 Specific objectives**

1. To compare PMC uptake (adherence) levels between community- versus health facility-based strategies
2. To determine whether SMS or Health Surveillance Assistant (HSA) reminder has additional benefit on PMC uptake (adherence) levels
3. To determine the safety of PMC delivery in the community versus in the health facility
4. To determine and compare the cost to the health service of delivering PMC using each individual delivery strategy
5. To determine and compare the cost to the patients and guardians of receiving PMC using individual delivery strategies
6. To determine the feasibility and acceptability of delivery of PMC in a typical Malawi health system setting

### **7.3 OUTCOMES**

#### **7.3.1 Primary outcome**

100% of PMC drugs uptake (defined as administration of **all** 3-day treatment courses, given 2, 6 and 10 weeks after discharge) assessed by unannounced spot checks

